#### Community follow-up

In the community follow-up assessing treatment failure rates, the EMPIC cluster randomised controlled trial (which included Bangladesh) reported a 5.4% treatment failure rate among children aged 7–59 days with fast breathing pneumonia [29] and a 4.3% failure rate among children aged 2–59 months with chest indrawing pneumonia [30]. Here, we will assume slightly higher treatment failure rates in real-life settings: 8% for children aged 7–59 days with fast breathing pneumonia, and 6% for children aged 2–59 months with chest indrawing pneumonia.

Using the standard formula for a single proportion, a 4% margin of error, and 95% confidence level, we arrive at a required sample size of 176 non-hypoxaemic young infants aged 7–59 days with fast breathing pneumonia for descriptive analysis per site. Assuming 5% loss to follow up, we will enrol a total of 185 non-hypoxaemic young infants with fast breathing aged 7–59 days, given oral amoxicillin within our study and followed up for outcome assessment at each district.

Lastly, using the standard formula for a single proportion with a 3% margin of error and a 95% confidence level, we calculated a required sample size of 238 non-hypoxaemic children aged 2–59 months with chest indrawing pneumonia per site. Assuming 5% loss to follow-up, we will enrol 250 non-hypoxaemic 2–59 months old children with chest indrawing pneumonia, given oral amoxicillin in our study and followed up for outcome assessment at each district.

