### Study settings, period, and population

We will select two *upazilas* (sub-districts) in total: one each from the Kushtia and Dinajpur districts. From them, we will choose 20 CCs based on service availability and caseload, in consultation with national and district-level health managers. Dinajpur district covers an area of 3437.98 km^2^ and is home to 299 0128 inhabitants, resulting in a population density of 868 people per km^2^ [35]. The district has one medical college hospital, one district hospital, 12 *upazila* health complexes (sub-district hospitals), 119 union sub-centres and union health & family welfare centres (union level health centres), and 337 CCs (health outpost centres) [36]. Kushtia district has a population of 1 986 838 and covers an area of 1621.15 km^2^, leaving a density of 1073 people per km^2^ [37]. The district's health facilities include one district hospital (secondary level referral hospital), five *upazila* health complexes (sub-district hospitals), 73 union health and family welfare centres (union level health centres), and 205 CCs [36]. The study will be conducted across 24 months, where 18 months will be reserved for the delivery of the implementation package.

The study population will be under-five children presenting with pneumonia in CCs, CHCPs working in CCs, caregivers and family members of children visiting CCs, district and sub-district level health managers and supervisors and central-level health managers and policymakers.

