### Sample size and sampling strategy

#### Household survey

Baseline data from the Bangladesh Health and Demographic Survey 2017–18 indicate a 40% care-seeking rate among children under five with suspected pneumonia in the four weeks preceding the survey [39]. Assuming a baseline value of care-seeking practice for childhood illness among children under five years of age with suspected pneumonia in the past four weeks is 40% in baseline and (based on our objectives) 80% in end-line, and setting a 5% margin of error and 95% confidence interval, the unadjusted sample size is 23 children under five years of age with suspected pneumonia per district, increasing to 58 after adjustment for a 20% non-response rate and a design effect of 2.0. To achieve this sample size, we will need to reach 5121 households and 20 480 population per district. For the household survey, we will use a stratified sampling technique to ensure equal representation. Specifically, we will select villages, considered as the primary sampling unit, through probability proportional to size sampling, after which we will identify and interview all women with under-five children in the sampled villages.

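### The ±4 and ±3 point per-district margins for treatment failure assume independent children, although the children are clustered within clinics

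*Protocol article*

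**What the plan says.** In the protocol article, Community follow-up (under Sample size and sampling strategy), the assumed failure rates are "8% for children aged 7–59 days with fast breathing pneumonia, and 6% for children aged 2–59 months with chest indrawing pneumonia". The young-infant calculation is described as "Using the standard formula for a single proportion, a 4% margin of error, and 95% confidence level" and ends with "we arrive at a required sample size of 176 non-hypoxaemic young infants aged 7–59 days with fast breathing pneumonia for descriptive analysis per site". The older-child calculation is "using the standard formula for a single proportion with a 3% margin of error and a 95% confidence level", and there "we calculated a required sample size of 238 non-hypoxaemic children aged 2–59 months with chest indrawing pneumonia per site". The only adjustment is for 5% loss: "Assuming 5% loss to follow up, we will enrol a total of 185 non-hypoxaemic young infants with fast breathing aged 7–59 days", and 250 older children, in each district. No design effect or ICC is mentioned.

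The section on study settings describes two upazilas, one per district, and says "From them, we will choose 20 CCs based on service availability and caseload". Table 3 identifies cases from facility registers, at union-level facilities as well as at CCs. In the same sample-size section, the household survey is adjusted for "a 20% non-response rate and a design effect of 2.0".

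**The concern.** Children treated at one clinic share the provider who classifies, treats and counsels them. They also share its drug supply and its local community. If failure is at all correlated within clinics, each child adds less information than an independent child would, and a margin from the simple formula is too optimistic. The authors allowed for clustering in the household survey but not here, and they do not say why.

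What is at stake is how firmly each district's failure rate can be read. Treatment failure is the clinical outcome that describes how children fare when treated at the clinic without referral, and the study is meant to inform scale-up.

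**Working it through.** **Inputs from the protocol article.** p = 0.08, margin 0.04, n = 176; p = 0.06, margin 0.03, n = 238; 95% confidence; 5% loss; 20 CCs over two districts.

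**Inputs assumed.** 10 CCs per district (the split is not stated), equal caseloads, no union-level facilities, and an ICC of 0.01 to 0.05.

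**Step 1: reproduce the plan's figures.** n = 1.96² × p(1−p) / margin².
- Young infants: 3.8416 × 0.0736 / 0.0016 = 176.7, printed as 176.
- Older children: 3.8416 × 0.0564 / 0.0009 = 240.7, printed as 238.
- Enrolment: 176 / 0.95 = 185.3 and 238 / 0.95 = 250.5, printed as 185 and 250.

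The figures therefore reproduce, to within about 1%, with a design effect of 1. Rounded up, the formula gives 177 and 241. A finite-population correction, n / (1 + (n−1)/N), with N = 20 480 (the household-survey population per district) gives 175.2 and 237.9, which round up to 176 and 238. That such a correction was used is an inference; the text does not state one.

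**Step 2: slack.** Margin = 1.96 × √(p(1−p)/n) gives ±4.01 points at n = 176 and ±3.02 at n = 238. Nothing is left to absorb a design effect.

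**Step 3: add clustering.** Design effect (DEFF) = 1 + (m−1) × ICC, with m = 176/10 = 17.6 and 238/10 = 23.8. Margin = 1.96 × √(p(1−p) × DEFF / n).

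| Assumption | DEFF, infants / older | Margin per district, infants / older (points) |
|---|---|---|
| ICC 0 | 1.00 / 1.00 | ±4.01 / ±3.02 |
| ICC 0.01 | 1.17 / 1.23 | ±4.33 / ±3.34 |
| ICC 0.02 | 1.33 / 1.46 | ±4.63 / ±3.64 |
| ICC 0.05 | 1.83 / 2.14 | ±5.42 / ±4.41 |
| DEFF 2.0 | 2.00 / 2.00 | ±5.67 / ±4.27 |

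A DEFF of 2.0 corresponds to an ICC of 1/16.6 = 0.060 for infants and 1/22.8 = 0.044 for older children. Unequal caseloads widen the margins further: with a coefficient of variation of 0.5 and ICC 0.02, they are about ±4.8/±3.8.

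**Step 4: few clusters.** With 10 clinics the t multiplier on 9 degrees of freedom is 2.262, which is 1.154 times 1.96. At DEFF 2.0 the margins become 5.67 × 1.154 = ±6.5 and 4.27 × 1.154 = ±4.9.

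**Step 5: pool the two districts.** n = 352 and 476. At DEFF 2.0 the standard errors are √(0.0736 × 2 / 352) = 2.04 points and √(0.0564 × 2 / 476) = 1.54 points. With z = 1.96 the margins are ±4.0 and ±3.0. With t on 18 degrees of freedom (2.101) they are ±4.3 and ±3.2.

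**The case against.** The strongest reply is that the size of the problem is unknown. The 2.0 was chosen for care-seeking in a survey with villages as sampling units, and nothing in the document shows that it applies to clinical failure among clinic attenders. At an ICC of 0.01 the margins are ±4.3/±3.3, which matters little for a descriptive analysis. Union-level facilities would add clusters and lower the design effect. The clinics are chosen purposively and the findings are declared specific to the selected upazilas; if inference is confined to those clinics as a fixed set, the inflation is smaller. The article also names no interval method, and that choice is commonly left to an analysis plan.

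Much of this stands. It rules out treating ±5.7/±4.3 as the true margins, and it rules out saying that the eventual intervals will be too narrow. It does not rescue the stated margins. The protocol itself attaches a number to each district, that number needs zero correlation, and more facilities would reduce the design effect without removing it. The fixed-set view also sits poorly with the aim of informing scale-up.

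A reader might also add the margins to the assumed rates and infer a safety claim that failure stays below about 12% or 9%. The document makes no such claim: it attaches no threshold, hypothesis or decision rule to the failure rate. Nor does the gap between 176/238 and 177/241 amount to a real shortfall; it changes the margins by 0.01 to 0.02 points.

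**Conclusion.** The point holds in limited form. The arithmetic is sound to within rounding or an unstated correction; the fault is the unstated assumption of independence. The per-district margins of ±4 and ±3 points hold only at an ICC of zero. With 10 equal clinics per district and z = 1.96, they become about ±4.3/±3.3 at ICC 0.01, ±4.6/±3.6 at 0.02 and ±5.4/±4.4 at 0.05. At a borrowed design effect of 2.0 they are ±5.7/±4.3 (±6.5/±4.9 with t on 9 degrees of freedom).

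These sizes rest on an ICC that the document does not give, an inferred clinic count and equal caseloads. It would be tempting to conclude that enrolment must double. That does not follow: the aim is descriptive, and the pooled sample gives about the printed margins even at a design effect of 2.0 with z. The correction is worth making because it is cheap and the same section already allows for clustering elsewhere.

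**What to change.** - Keep the enrolment targets of 185 and 250 per district.
- Restate the per-district margins as a range over a stated ICC or design effect, with the number of facilities assumed. At the least, say that ±4 and ±3 assume no clustering.
- Give the pooled two-district margin as the more precise estimate, with its assumption: at design effect 2.0, about ±4.0/±3.0 with z or ±4.3/±3.2 with t on 18 degrees of freedom.
- Compute confidence intervals for failure rates with the facility as cluster, using the same reference distribution as the stated margins. Quoting z-based margins and then analysing with t would again promise more than is delivered.
- Minor: change 176 and 238 to 177 and 241, or state the finite-population correction and its population if one was used.

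The cost is a few sentences and one analysis option, with no extra children. The downside is that the stated precision for each district becomes less favourable.

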## METHODS

The goal of this study is to achieve high and effective population coverage of pneumonia treatment in under-five children in Bangladesh and to develop a scalable implementation strategy for contextual adaptation to other low- and middle-income countries (LMICs).

Our primary objective is to increase access to pneumonia treatment in under-five children to achieve high (≥80%) and effective population-based coverage (*i.e.*, patients receiving the full course of pneumonia treatment) in the study area. We also set five secondary objectives:

to increase care-seeking practices from appropriate healthcare providers for general danger signs and pneumonia-related signs of under-five children;to determine the rate of clinical treatment failure of young infants 7–59 days old with fast breathing and children 2–59 months old with fast breathing and/or chest indrawing pneumonia who received treatment from CHCPs;to assess the compliance with pneumonia treatment among young infants 7–59 days old with fast breathing and children 2–59 months old with fast breathing and/or chest indrawing pneumonia who received treatment from CHCPs;to explore the knowledge, perceptions, and experiences of health facility staff, CHCPs, and beneficiaries on the implementation of pneumonia management;to improve the availability of essential commodities in the CCs to manage pneumonia in under-five children.

We will achieve these objectives through three activities: designing an implementation delivery package for introducing the EMPIC in Bangladesh (activity 1); employing a continuous learning process during the implementation period to understand the prerequisites for the scale-up of the package (activity 2); and assessing whether the implementation delivery package worked by documenting the implementation process, understanding and assessing care practices, and exploring the experiences of health managers, health service providers, and caregivers related to the implementation of the package (activity 3).

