### Study outcome

The primary outcome of interest is high (≥80%) and effective (patients receiving the full course of pneumonia treatment) coverage among under-five children (**Table 3**). The secondary outcome of interests are: treatment failure rate among young infants 7–59 days old with fast breathing and children 2–59 months old with chest indrawing and/or fast breathing pneumonia who received treatment from CCs; availability of essential commodities and supplies for managing childhood pneumonia; CHCPs’ knowledge of managing childhood pneumonia; caregiver’s knowledge and care-seeking practices regarding childhood pneumonia; and prevalence of pneumonia among under-five children, utilisation of CCs for pneumonia related symptoms; and treatment compliance.

**Table 3 T3:** Study enrolment and outcome assessment strategy

Activity	What	Who	When	Where	How
Case identification	Identify young infants with fast breathing pneumonia and children aged 2–59 months with fast breathing and/or chest indrawing pneumonia from data extracted from the service registers	Trained data extractors appointed by the study team	Twice in a week	Health facilities (CCs and union-level health facilities)	Trained data collectors will extract data from the registers or case record forms in the health facilities. From there, they will identify young infants with fast breathing pneumonia and children aged 2–59 months with fast breathing and/or chest indrawing pneumonia. They will provide this information to study-appointed nurses/paramedics who will conduct enrolment of the participants.
Screening and Enrolment	Enrol eligible young infants and children aged 2–59 months based on inclusion and exclusion criteria	Study appointed nurses or paramedics	One to three days after facility visit	Phone	Nurses and paramedics will screen the children based on the inclusion and exclusion criteria from the information received from study-appointed data extractors. They will contact the caregivers of the eligible children over the phone and take verbal consent for the home visit. They will enrol the children if consent is given by the caregivers.

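### The 2–59-month follow-up is sized for chest indrawing only, but the outcome and enrolment table also admit fast-breathing-only children, and Table 3 adds union-level facilities that the outcome leaves out

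*Protocol article*

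**What the plan says.** Under Sample size and sampling strategy, the Community follow-up section plans the 2–59-month group on chest indrawing alone. It starts from "a 4.3% failure rate among children aged 2–59 months with chest indrawing pneumonia" in the earlier trial and assumes "6% for children aged 2–59 months with chest indrawing pneumonia" for routine conditions. The number required is found "using the standard formula for a single proportion with a 3% margin of error and a 95% confidence level", which gives 238 per site. After 5% loss to follow-up, "we will enrol 250 non-hypoxaemic 2–59 months old children with chest indrawing pneumonia" in each district. The section names no facility type.

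Elsewhere the population is wider:

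- The failure and compliance objectives (Methods) cover "children 2–59 months old with fast breathing and/or chest indrawing pneumonia who received treatment from CHCPs".
- The failure outcome (Study outcome) covers "children 2–59 months old with chest indrawing and/or fast breathing pneumonia who received treatment from CCs".
- The case-identification row of Table 3 looks for "children aged 2–59 months with fast breathing and/or chest indrawing pneumonia from data extracted from the service registers".
- The failure definition after Table 3 counts persistence of either sign on day 7 in this age group.

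On setting, Table 3 gives "Health facilities (CCs and union-level health facilities" as the place for case identification and for treatment documentation. Its follow-up row also refers to both facility types. The outcome is limited to treatment from CCs and the objectives to treatment from CHCPs, who staff the CCs according to the introduction. Activity 3 times follow-up from the CC visit, and Other data collection methods describes register extraction in CCs only.

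**The concern.** The sample size is derived for one population and the outcome is defined on a larger one. Children aged 2–59 months with fast breathing only belong to two objectives, the failure outcome and the enrolment flow, yet the plan gives them no expected rate, no number and no stated status. A field team working from Table 3 would enrol them. A team working from the sample-size section would count only chest indrawing. The article does not say which rule governs the 250.

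The distinction matters for interpretation. The Discussion says that under the previous iCCM protocol children of this age with fast breathing alone already received oral amoxicillin, while those with chest indrawing were referred. Treating chest indrawing without referral is therefore the changed element in this age group, and it is the group the sample size was built for. Box 1 puts both signs into one pneumonia class, so separation by sign will not happen unless someone asks for it.

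The setting mismatch is smaller but similar. Union-level cases would be identified, documented and followed, although they fall outside the objectives and the outcome.

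**Working it through.** **Inputs from Community follow-up.** p = 0.06, d = 0.03, 95% confidence (z = 1.96), 238 required, 5% loss, 250 enrolled per district.

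**Step 1: reproduce the plan's figures.** n = z²p(1−p)/d² = 1.96² × 0.06 × 0.94 / 0.03² = 240.7, so 241 against the stated 238, a difference of about 1%. For loss to follow-up, 238/0.95 = 250.5 and 238 × 1.05 = 249.9, against the stated 250. The half-width at 238 is 1.96 × √(0.06 × 0.94/238) = 3.0 points. I raise nothing against the arithmetic.

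**Step 2: two readings of the 250.**

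- *A chest-indrawing quota, with fast-breathing-only children added on top.* The ±3.0 points is kept, provided the chest-indrawing rate is reported separately. The fast-breathing-only children then have no planned number.
- *The total 2–59-month enrolment under Table 3's criteria.* Chest-indrawing children are only a share s of the 238 evaluable, and the half-width is 1.96 × √(0.06 × 0.94/(238s)).

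**Step 3: size under the second reading.** The documents do not give s, so the values below are assumptions that show the range.

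| Assumed share s | Evaluable with chest indrawing (238 × s) | 95% half-width at 6% | Total enrolment needed for 250 with chest indrawing (250/s) |
|---|---|---|---|
| 100% | 238 | ±3.0 points | 250 |
| 75% | 178.5 | ±3.5 points | 334 |
| 50% | 119 | ±4.3 points | 500 |
| 25% | 59.5 | ±6.0 points | 1000 |

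**Step 4: what a combined rate would show.** The combined rate is s × (chest-indrawing rate) + (1−s) × (fast-breathing-only rate). The documents give no fast-breathing-only rate, so these values are also assumptions. With s = 50% and chest indrawing at 6%:

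- fast-breathing-only at 2%: 0.5 × 6% + 0.5 × 2% = 4.0%
- at 6%: 6.0%
- at 8%: 0.5 × 6% + 0.5 × 8% = 7.0%

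The combined rate can therefore lie below, at or above the chest-indrawing rate. As an example of masking, with s = 30%, chest indrawing at 10% and fast-breathing-only at 4%, the combined rate is 0.3 × 10% + 0.7 × 4% = 5.8%. That would look in line with the planned 6% while the chest-indrawing rate was well above it.

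**Step 5: setting.** Three rows of Table 3 (case identification, treatment documentation, follow-up) name CCs and union-level facilities. The outcome names CCs, the objectives CHCPs, Activity 3 the CC visit, and Other data collection methods CCs. The table is the only one of these that is wider.

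**The case against.** The strongest reply is that the sample-size section already answers the question: read literally, its 250 are children with chest indrawing. If fast-breathing-only children are enrolled in addition, the stated precision survives, and the losses in the table above arise only if that section is not followed. This stands, and it is why those losses are conditional. It does not remove the mismatch, because the outcome and Table 3 are equally plain in the other direction. Table 3 refers to inclusion and exclusion criteria that the article does not list. They may settle who is enrolled, but if they restricted enrolment to chest indrawing they would leave part of the stated outcome population unobserved.

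A second reply is that reporting by sign belongs to an analysis plan that is not shown. That is also fair. The Data analysis section speaks of failure rates in the plural, and the young infants and the chest-indrawing children are sized separately. A reader might infer that only one pooled rate will be reported, but no section says so. Even so, an analysis plan cannot supply chest-indrawing children who were never enrolled. The counting rule has to be settled at enrolment.

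Two further inferences are tempting and unsupported. One is that pooling dilutes the failure rate: without a case mix or a fast-breathing-only rate, the direction is unknown. The other is that the outcome itself includes union-level cases: it is limited to CCs, and the conflict is with Table 3 alone.

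Finally, fast-breathing failure may be of interest in its own right, since the introduction says the current service model starts at union level and needs extending to CCs. Including these children is a legitimate choice. The objection is only to leaving their status undefined.

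**Conclusion.** The point holds as an internal inconsistency on a descriptive secondary outcome. The 6% rate, ±3-point margin and 250 per district apply to chest indrawing, while the objectives, outcome, enrolment table and failure definition describe a mixed population to which those figures do not apply. Nothing is planned for fast-breathing-only children, and Table 3's setting is wider than the outcome's.

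The cost depends on how the 250 is counted. As a chest-indrawing quota with separate reporting, nothing is lost. As a mixed total, the chest-indrawing margin becomes about ±3.5 to ±6.0 points for assumed shares of 75% down to 25%, with 238 evaluable and 6% failure. A combined rate could also hide the chest-indrawing result, without a predictable direction. The shares and the fast-breathing-only rates are assumptions; the mismatch of populations and settings is in the text. It should be corrected before enrolment.

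**What to change.** 1. State in Table 3 and in the outcome that the 250 per district counts only non-hypoxaemic children aged 2–59 months with chest indrawing, with or without fast breathing, treated at CCs. The sign restriction is already in the sample-size section, and the CC restriction is already in the outcome.
2. Report treatment failure and compliance separately for three groups: 7–59 days with fast breathing; 2–59 months with chest indrawing; 2–59 months with fast breathing only. Label the third as descriptive, with no stated precision.
3. Remove union-level facilities from Table 3, or report those cases as a separate group outside the outcome.

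The change is mostly wording. It requires presenting sign and treating facility to be recorded for each enrolled child, which the authors should confirm the extraction tool does. The price is slightly more reporting and possibly a limit on how many fast-breathing-only children receive study follow-up visits, to contain the workload.
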